### End of study

The study will be terminated when the participant reaches skeletal maturity, defined as less than 1.0 cm growth of body height in six months, or if the curve progresses more than 6 degrees, compared to the baseline radiograph, seen on two consecutive spinal standing radiographs. In case of curve progression and a Cobb angle surpassing 25 degrees, treatment will be offered with standard TLSO or nighttime brace to be worn 20 hours and 8 hours, respectively, per day. In the event that a Cobb angle surpasses 45 degrees with risk for further progression, patients will be offered surgical treatment. Follow-ups will be done in similar way also for those failing treatment. Post-treatment follow-up after endpoint is planned to occur at 2, 5 and 10 years prospectively including full spinal frontal and sagittal radiographs.

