### Randomization procedure

After assessment, patients fulfilling the inclusion and exclusion criteria will be asked to give written and signed consent for participation. If the patient is aged less than 15 years, parental consent is also required. Patients who decline participation will be monitored as part of clinical routine.

Randomization will be done in a 1:1 ratio. Randomization will be performed using an online module available through the Swedish spine register (www.swespine.se). Randomization sequence have been prepared by an independent data manager at MedScinet (www.medscinet.com), the company that runs the register platform, and is unknown to the researchers.

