### Data analysis

Data from the trial will be compared based on the ’intention to treat’ principle. An intention to treat (ITT) analysis means that all patients, regardless of non-compliance, loss to follow-up or drop-out, remain in the analysis of the group to which they were randomized [17]. Depending on the mechanisms for missing data, the most relevant imputation method considering missing at random or not missing at random will be used in the ITT analysis [18]. A causal survival analysis measuring complier average causal effects (CACE), where standardization of baseline covariates (age, sex, Risser sign, major curve) and inverse probability weighting of post-randomization treatment adherence data is used in a per protocol analysis, to be contrasted with ITT results [19]. With basis in the COM-B model, patient reported capability and motivation can be hypothesized as potential mediators of treatment effect on the outcome variables. Fig 3 summarizes these causal inferences in a direct acyclic graph (DAG) model [20]. If a patient fails treatment and is offered another treatment, such as brace or surgery, the Cobb angle at the moment of commencing this treatment will be considered in the secondary outcome analysis of Cobb angle. Categorical parameters will be compared by the Chi-square test. Continuous and discrete parameters will be measured using parametric or non-parametric tests (depending on skewness) for group comparisons. Individual variables will be tested for their association with treatment effect by adding a predictor × treatment group interaction term to a regression equation. Additionally, Kaplan-Meier survival analyses will be used to display the probability of more than 6° Cobb progression over time. Cox regression or pooled logistic regression will be used to provide survival hazard ratios. The results will be reported according to Consolidated Standards of Reporting Trials (CONSORT) [21].

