### Power analysis

The end point failure of treatment is defined as an increase of the Cobb angle of more than 6° on two consecutive x-rays, when compared to the x-ray performed at time of inclusion. Based on a hypothesized failure rate of 10% in the scoliosis specific exercise group and 39% in the observation group [6], with a significance level of 5% and a power of 80% and consideration for dropout of up to 20% and an additional adding of five individuals per group, an estimated number of 45 individuals in each group is required.

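### In ordinary use, the planned Kaplan-Meier display would read higher than the proportion of children who progress before skeletal maturity; cumulative incidence fits this design better

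*Protocol article*

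**What the plan says.** The Data analysis section compares categorical outcomes by chi-square test and then adds a time-to-event display: "Kaplan-Meier survival analyses will be used to display the probability of more than 6° Cobb progression over time". For the relative effect it says: "Cox regression or pooled logistic regression will be used to provide survival hazard ratios". It does not say how a child who matures without progressing enters either analysis.

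The End of study section says: "The study will be terminated when the participant reaches skeletal maturity, defined as less than 1.0 cm growth of body height in six months". The other way to end is confirmed progression. The Outcome measurements section schedules spine films yearly and clinical visits half-yearly up to maturity, and allows extra films when progression is suspected. Under Subjects, entry is open from 9 to 15 years of age, so time from entry to maturity will differ between children.

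The Power analysis section works with crude proportions, a "hypothesized failure rate of 10% in the scoliosis specific exercise group and 39% in the observation group".

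**The concern.** Kaplan-Meier knows two outcomes, event or censored. It assumes that a censored child goes on to progress at the rate of the children still under observation. That is reasonable for a child lost to follow-up. It is less reasonable for a child whose growth has ended, because the protocol itself ties the need for observation and bracing to remaining growth. If matured children are censored, one minus the curve describes the risk had nobody stopped growing. A reader of a figure labelled as the probability of progression will take it for the share of children who progress before maturity.

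The late part of the curve is where a reader looks for risk by the end of growth. Both arms would read too high there, and the absolute gap between them would look wider than the crude proportions in the same report.

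A smaller matter is that the plan treats Cox and pooled logistic regression as two routes to one hazard ratio. With its usual logit link, the pooled model gives a discrete-time odds ratio.

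**Working it through.** **1. The plan's own figure.** Inputs from the Power analysis section are 10% and 39%, "with a significance level of 5% and a power of 80" per cent, then "consideration for dropout of up to 20% and an additional adding of five individuals per group". I assume a two-sided test. The arcsine formula gives

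- h = 2·asin(√0.39) − 2·asin(√0.10) = 1.349 − 0.644 = 0.705
- n = 2·(1.960 + 0.842)² / h² = 15.70 / 0.498 = 31.5, so 32 per arm
- 32 / 0.8 = 40, and 40 + 5 = 45

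This matches "an estimated number of 45 individuals in each group is required". The calculation uses crude proportions, so the Kaplan-Meier point does not touch it.

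**2. End of the curve against the proportion progressing.** Assumptions, none of them in the documents: 39% and 10% are before-maturity proportions, the progression hazard λ is constant, time to maturity is uniform on (a, b) years and independent of progression, and nobody is lost.

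- Proportion progressing before maturity: F = 1 − (e^(−λa) − e^(−λb)) / (λ(b − a)). Set F to 0.39 or 0.10 and solve for λ.
- One minus Kaplan-Meier at the end, with maturity censored: 1 − e^(−λb).

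Example, observation arm, maturity over 1–3 years: λ = 0.2524 gives F = 1 − (0.7769 − 0.4690)/0.5048 = 0.39, and the curve ends at 1 − e^(−0.757) = 0.53.

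| Maturity (years) | λ, observation | Curve end (true 0.39) | λ, exercise | Curve end (true 0.10) | Displayed difference (true 0.29) |
|---|---|---|---|---|---|
| 1–3 | 0.252 | 0.53 | 0.053 | 0.15 | 0.38 |
| 1–4 | 0.204 | 0.56 | 0.042 | 0.16 | 0.40 |
| 2–5 | 0.143 | 0.51 | 0.030 | 0.14 | 0.37 |

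The lower end of the range comes from the yearly film schedule. If each child's last film is the first annual one at or after maturity, the 2–5 year spread becomes last films at 3, 4 or 5 years, one third each. Solving 1 − (e^(−3λ) + e^(−4λ) + e^(−5λ))/3 = 0.39 gives λ = 0.125 and a curve end of 0.46. For 0.10, λ = 0.026 and the curve ends at 0.12. The 1–3 year spread under the same rounding gives 0.45 and 0.12, so the lower end is approximate.

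**3. Early follow-up.** At two years, one minus Kaplan-Meier and cumulative incidence in the observation arm are 0.396 and 0.355 (1–3 years), 0.335 and 0.311 (1–4 years), and 0.249 and 0.249 (2–5 years). The gap is 0 to 0.04. It opens only as children mature.

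**4. Logit link.** Hazard ratio, observation to exercise: ln 0.61 / ln 0.90 = 0.494 / 0.105 = 4.69. With k equal intervals the risks per interval are 1 − 0.61^(1/k) and 1 − 0.90^(1/k).

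| Intervals | Risks per interval | Odds ratio | Excess over 4.69 |
|---|---|---|---|
| 2 annual | 0.219, 0.051 | 5.18 | 10% |
| 3 annual | 0.152, 0.035 | 5.01 | 7% |
| 4 half-yearly | 0.116, 0.026 | 4.93 | 5% |
| 6 half-yearly | 0.079, 0.017 | 4.85 | 3% |

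In a large simulation with annual films, a complementary log-log link returned 0.212 for a true hazard ratio of 0.213 (exercise to observation). The logit link returned 0.193.

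**The case against.** A reader might infer that the protocol censors matured children. It does not say so, and a separate analysis plan could keep them event-free, which would remove the overstatement. That stands, and the point is therefore conditional on ordinary use. It is still more than a missing detail, because the article names both the estimator and the quantity it should show, and the design makes the two diverge by default.

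A reader might also infer that the primary comparison is biased. The documents do not support this. Kaplan-Meier is an additional display, categorical outcomes go to chi-square, the sample size rests on crude proportions, and a Cox model with maturity censored gives an interpretable cause-specific hazard ratio.

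The figures rest on assumptions. The Power analysis section gives no time horizon for its 10% and 39%, and nothing in the article gives the distribution of time to maturity. The widest gap is at the end of the curve, where few children remain at risk. All of this stands.

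It can further be said that maturity is a stopping rule and does not make a later increase in Cobb angle impossible, and that films are planned 2, 5 and 10 years after the endpoint. That is true, but those films are not tied to this analysis. The choice is then one of estimand, and a Kaplan-Meier curve would need a label saying that it is conditional on continued growth.

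On the logit link, 3–10% is small beside sampling error. With 45 per arm the expected events are 0.39 × 45 = 17.6 and 0.10 × 45 = 4.5. The standard error of the log hazard ratio is about √(1/17.6 + 1/4.5) = 0.53, a factor of about 2.8 either way at 95%. Cox is also already named as the alternative, so this remains a side remark.

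**Conclusion.** The point holds for the display. With follow-up ending at individually varying maturity, ordinary Kaplan-Meier would not show the proportion who progress before maturity. Under the assumptions above, the observation curve would end at about 0.46–0.56 where 39% progress and the exercise curve at about 0.12–0.16 where 10% do, with little discrepancy in the first two years. Direction follows from the design once matured children are censored; size depends on the assumed maturity times and hazard. A spread as wide as 0.5–4 years would end at 0.60 and 0.17.

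The documents do not support saying that the trial's test, its sample size or a cause-specific Cox hazard ratio is wrong. That pooled logistic regression does not give a hazard ratio is correct in the strict sense, but the difference is minor here.

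**What to change.** - Plot cumulative incidence of progression by arm (Aalen-Johansen) with skeletal maturity as a competing event. Keeping matured children event-free to the end of the time axis gives the same curve if nobody is lost.
- Censor only true loss to follow-up, and state this rule.
- Choose one hazard model in advance. If it is a pooled discrete-time model, use a complementary log-log link. Describe the hazard ratio as cause-specific.

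The cost is a change of wording, a different estimator for one figure and slightly more analysis work. No new data are needed. The displayed difference will look less dramatic, but it will agree with the crude proportions in the same report.

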**Fig 3 pone.0285246.g003:**
[figure not shown]
Directed acyclic graph of hypothesized mechanisms in single mediator models in the PREMISCOPRO trial and the estimated averaged effects standardized for baseline covariates and inverse probability weighted for post-randomization treatment adherence confounding. The indirect effect (*ab*-product) is the average intervention effect through the mediator. *a*, a-path (the intervention-mediator effect); *b*, b-path (the mediator-outcome effect); *c*, c-path (the total effect of the intervention on the outcome, without accounting for potential mediator); c′ (the direct effect of the intervention on the outcome, that works through all other mechanisms excluding the selected potential mediator).

### Power analysis

The end point failure of treatment is defined as an increase of the Cobb angle of more than 6° on two consecutive x-rays, when compared to the x-ray performed at time of inclusion. Based on a hypothesized failure rate of 10% in the scoliosis specific exercise group and 39% in the observation group [6], with a significance level of 5% and a power of 80% and consideration for dropout of up to 20% and an additional adding of five individuals per group, an estimated number of 45 individuals in each group is required.

## Discussion

This multicenter study on exercise treatment with an active self-corrective strategy for mild idiopathic scoliosis will determine effectives compared with observation alone. The project includes key methodological features in order to minimize bias in clinical trials such as true randomization, specification of eligibility criteria, blinding and intention-to-treat analysis. The methodological framework of this project is similar to a successfully managed randomized, but yet unpublished, trial from our group [22].

Our choice of outcomes and inclusion criteria is in line with recommendations for clinical trials studying idiopathic scoliosis. Scoliosis-specific exercises, as of today, are not routinely prescribed for scoliosis patients in Swedish healthcare. The mainstay for mild scoliosis is observation during growth. Our choice to use an active self-correction strategy is based on an impartial approach to synthesizing a broad intervention covering principles outlined in scoliosis specific exercise literature. This approach has been used successfully in randomized trials previously [6, 22]. We believe that adolescents who can actively manage their scoliosis, with proper education and information about the condition, will have better patient-reported outcomes in terms of increased self-esteem (mental health and self-image) and self-empowerment (capability and motivation).
